The second objective is to examine whether effects of mindfulness and fantasizing on PC in rMDD individuals differ from ND individuals. To this end, 50 ND participants will be matched to the rMDD participants and similarly randomized to undergo both mindfulness and fantasizing interventions. Comparing the effects of interventions in both rMDD and ND individuals allows us to study whether therapeutic techniques, developed and often studied in a clinical sample, work similar or different in ND individuals. Since most studies focus on the effects of mindfulness and positive fantasizing in a clinical sample [16, 19, 27, 28, 42], we hypothesize these techniques to be effective in reducing PC in rMDD individuals but expect that the interventions may show different effects on PC in ND individuals.

The third objective is to examine in an exploratory manner whether individual characteristics affect the effectiveness of the two interventions in reducing PC across all participants (i.e., what works for whom). We know from the previous literature that there is substantial variability in treatment response between MDD individuals [43,44﻿]. This variability has been suggested to be related to individual characteristics such as depressive symptoms and history, comorbid disorders/symptoms, personality traits, and cognitive dysfunction. For example, people with anhedonia may have a harder time to engage in positive fantasizing, and people with lower levels of executive functioning (mental flexibility) may find mindfulness practice difficult. Whether these independent predictors of depressive vulnerability affect intervention effects is interesting for personalized treatment purposes. This objective is exploratory, and hence we do not have specific hypotheses about the direction of these effects.

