## Outcome measures

### Study aim 1

Primary outcomes for the first study aim in which we will examine changes in the content and dynamics of PC after interventions are within-subject changes, comparing pre- and peri-intervention measurements, in 1) self-reported measures of the content and dynamics of PC measured with ESM and the SART (using the following variables: rumination, occurrence of off-task thinking, valence of thoughts, temporal orientation of thoughts, self-relatedness of thoughts, and stickiness of thoughts), 2) HR and HRV during PC (i.e., negative, repetitive thinking) measured with ECG during ESM self-reports, and 3) EEG characteristics during PC measured in the context of the SART.

Secondary outcome measures that will be used to explore the role of sleep on the effectiveness of interventions in reducing the vulnerability for depressive relapse are 1) within-subject changes in objective and subjective sleep (measured as total sleep time, sleep quality, sleep onset latency) using actigraphy and ESM items about sleep and 2) within-subject changes in PC following the interventions. Moreover, we will examine changes in (residual) depressive symptoms and other depression-related measurements before and after the interventions (for questionnaires see Procedure) using within-subject comparisons.

### Study aim 2

To test whether changes in PC induced by fantasizing and mindfulness are different in rMDD versus ND participants, primary outcome measures are between-group differences in individual changes between pre- and peri-intervention measurements for both interventions (fantasizing and mindfulness) measured with 1) self-reported PC measures (ESM and SART), 2) HR and HRV during self-reported PC (ESM), and 3) EEG characteristics during PC measured with the SART.

### Study aim 3

Baseline individual characteristics of 100 participants (both ND and rMDD) for examining the magnitude of changes in PC following interventions include: 1) self-reported measures of PC measured with ESM and the SART, 2) HR and HRV measured with ECG during self-reported PC measured with ESM, 3) EEG characteristics during PC measured with the SART, and 4) resting state EEG. Predictors include mindfulness, rumination, emotion regulation strategies, psychiatric history, personality, dysfunctional attitudes, and childhood trauma.

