To address the secondary objective about the role of sleep on the effectiveness of interventions in reducing PC, we will be using LMEs or GAMs depending whether the data are nonlinear. If sleep plays a role in whether interventions reduce PC, we expect to find a main effect of sleep (i.e., total sleep time, sleep quality and sleep onset latency) on changes in self-reported PC after the interventions.

To study the effects of the interventions on depressive symptoms using self-report questionnaires, a repeated measures ANOVA will be used with questionnaire scores (IDS-SR, PTQ, RPA, ERQ, FFMQ, LARSS, PANAS) administered as dependent variable and intervention (fantasizing or mindfulness) and session (pre- or peri-intervention) as independent variables. If interventions differentially affect depressive symptoms, we expect to find an interaction effect between intervention and session.

### Study aim 2

To study whether changes in PC by fantasizing and mindfulness are different in individuals with rMDD vs. ND controls, we will run the same analyses as for study aim 1, but with the variable group (rMDD or ND) added as an independent variable. Specifically, to examine the differential effects of self-reported PC, HR(V), and EEG, we will include session and intervention in interaction with group as independent variables in the model. If changes in PC after interventions are different in rMDD vs. ND individuals, we expect to find an interaction effect between group, session, and intervention on self-reported PC and its (neuro)physiological correlates measured with HR(V) and EEG.

### Study aim 3

For the third objective of exploring the role of individual characteristics on the effectiveness of the interventions at reducing PC, we will use baseline individual characteristics of participants assessed by means of a set of questionnaires (e.g., mindfulness, rumination, emotion regulation strategies, psychiatric history, personality, dysfunctional attitudes, childhood trauma etc.) and correlate those with changes in 1) self-reported measures of PC measured with ESM and the SART, 2) HR and HRV during reported PC, and 3) EEG characteristics during PC measured with the SART after mindfulness and positive fantasizing interventions. When significant correlations are found, we will do post-hoc moderation analyses to see how specific individual characteristics moderate changes in PC.

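### Aim 2 names only the group × session × intervention term as the sign that changes in PC differ between groups, but that term is zero when the rMDD–ND gap is the same for both techniques

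*Protocol article*

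**What the plan says.** Four places in the protocol article bear on aim 2.

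- **Background, second objective.** The aim is to "examine whether effects of mindfulness and fantasizing on PC in rMDD individuals differ from ND individuals". The hypothesis is "we hypothesize these techniques to be effective in reducing PC in rMDD individuals but expect that the interventions may show different effects" in ND participants.
- **Outcome measures, Study aim 2.** The "primary outcome measures are between-group differences in individual changes between pre- and peri-intervention measurements for both interventions", measured by self-report (ESM and SART), HR/HRV and EEG.
- **Statistical analyses, Study aim 2.** On the model: "we will include session and intervention in interaction with group as independent variables in the model". On what would show a group difference: "If changes in PC after interventions are different in rMDD vs. ND individuals", then "we expect to find an interaction effect between group, session, and intervention on self-reported PC" and on its physiological correlates.
- **Statistical analyses, closing paragraph.** P-values are Benjamini–Hochberg corrected. Non-significant LME effects are followed by Bayes Factors, to judge whether they support the null.

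The Sample size section also justifies 50 per group for aim 2 by a two-group t-test, and says this gives enough power for group differences in change.

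**The concern.** The objective, the primary outcome and the sample-size argument all ask whether the pre-to-peri change differs between rMDD and ND. That is a group × session question, which can be asked for each technique or averaged over the two. The analysis section ties the same question to a different term. The three-way interaction asks whether the contrast between techniques differs by group.

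If both techniques help rMDD participants more than ND participants by about the same amount, there is a real group difference of the kind the primary outcome describes, and the named term does not show it. The Bayes Factor step adds to the risk. A true zero in the three-way term could be reported as positive support for no difference, when it supports only the absence of a group-specific difference between techniques.

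**Working it through.** **Contrasts.** Write rF, rM for the mean pre-to-peri change in rMDD under fantasizing and mindfulness, and nF, nM for the same in ND.

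- Three-way = (rF − rM) − (nF − nM) = (rF − nF) − (rM − nM)
- Group × session, averaged = (rF + rM)/2 − (nF + nM)/2

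The second form of the three-way term shows the point: it is the rMDD–ND gap under fantasizing minus the gap under mindfulness. Equal gaps give zero, with no assumption about SDs or correlations.

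| Scenario (rF, rM; nF, nM), SD units | Three-way | Group × session |
|---|---|---|
| −0.59, −0.59; 0, 0 | 0 | −0.59 |
| −0.59, −0.59; −0.20, −0.20 | 0 | −0.39 |
| −0.70, −0.48; 0, 0 | −0.22 | −0.59 |
| −0.59, −0.30; 0, 0 | −0.29 | −0.445 |
| −0.59, −0.59; 0, −0.59 | −0.59 | −0.295 |

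The 0.59 is borrowed from the aim 1 planning effect, and the other values are illustrative. The last row is a case that the three-way term serves well.

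**The plan's own figure.** The article gives no power for either interaction. Its aim 2 calculation is a two-tailed t-test at d = 0.686 and 80% power, stated as 28 per group. The noncentral t gives 35 two-tailed and 27 one-tailed. That mismatch is a separate matter and does not affect this point.

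**Illustrative power.** Inputs:

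- a gap of 0.686 SD for both techniques (in the article this is a baseline rumination difference, so using it as a difference in change is an assumption);
- change SD 1 (assumed);
- correlation ρ between a participant's two change scores (not given in the article, so a range is shown);
- two-tailed 0.05, with 50 per group for self-report and 25 per group for HR/HRV and EEG (section on COVID-19 changes).

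Formulas: Var[(dF + dM)/2] = (1 + ρ)/2 and Var(dF − dM) = 2(1 − ρ). The standardised group × session effect is therefore 0.686/√((1 + ρ)/2), which is 0.970 at ρ = 0 and 0.792 at ρ = 0.5.

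| ρ | Group × session, 50 per group | Group × session, 25 per group | Three-way, equal gaps |
|---|---|---|---|
| 0 | 99.8% | 92% | 5% |
| 0.5 | 97.5% | 78% | 5% |

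A simulation with 0.59 SD in rMDD and 0 in ND (50 per group, 5,000 runs, ρ from 0 to 0.7) agrees: the three-way test rejected in about 5% of runs and group × session in 89–99%.

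**Unequal gaps.** If the two gaps differ by 0.343 SD, three-way power with 50 per group is 22% at ρ = 0, 40% at ρ = 0.5 and 59% at ρ = 0.7.

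**Precision.** The SE ratio (three-way to group × session) is √[2(1 − ρ)] / √[(1 + ρ)/2] = 2√[(1 − ρ)/(1 + ρ)]. It is 2.0 at ρ = 0, 1.15 at 0.5, 1.0 at 0.6 and 0.84 at 0.7. The three-way term has the larger standard error only when ρ is below 0.6.

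**The case against.** The strongest reply is that the three-way term is what this trial is about. The abstract words aim 2 in terms of mechanisms of change. The Background expects fantasizing to work through positive affect and thought content, and mindfulness through present focus. The aim 1 analysis predicts a shift to present-oriented thought under mindfulness only. For valence or temporal orientation, a technique effect present in rMDD and absent in ND does produce a three-way interaction. This stands, and it is why the term should stay. It does not cover outcomes that both techniques may move in the same direction, such as rumination or stickiness, and it does not test the primary outcome as defined.

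A second reply is that group × session is probably in the model already as a lower-order term, and that the article states an expectation, not a sole criterion. This also stands in part. A reader might infer that the trial will declare no group difference whenever the three-way term is null. The article does not say so. What it does is name no other term as the sign of a group difference.

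A reader might also infer that the term vanishes whenever both techniques work in rMDD and neither works in ND. That needs equal reductions; with unequal ones the term picks up the inequality and misses the shared part. Nor does the article predict no effect in ND, only that effects there may differ.

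Third, group × session has its own weakness. There is no untreated arm and the groups are not randomised, so group differences in drift or in reactivity to intensive sampling would enter it. The three-way term subtracts any shift common to both techniques. This is a fair reason not to make group × session the single primary test, but not a reason to leave it unnamed.

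**Conclusion.** The inference in the Study aim 2 analysis is wrong as written. A group difference in change does not imply a three-way interaction, and with equal gaps the three-way term is exactly zero. That result is algebra and rests on no assumption. The named term therefore does not match the primary outcome, which is a group difference in change for both interventions.

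The power figures only illustrate the size: about 97–99.8% (50 per group) or 78–92% (25 per group) for group × session, against 5% for the three-way test. They depend on the assumed 0.686 SD gap for both techniques, change SD 1 and correlation of 0 to 0.5. The article does not support the stronger claims that the three-way term is the wrong test for aim 2 as a whole, or that it is always the less precise one.

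**What to change.** In Statistical analyses, Study aim 2:

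1. Name group × session as an aim 2 test of whether changes in PC differ between rMDD and ND. Report it averaged over interventions and within each intervention, with confidence intervals.
2. Keep group × session × intervention as the test of whether the difference between techniques is group-specific, and reword the sentence so that it is tied to that question only.
3. List all of these tests in the Benjamini–Hochberg family.
4. State that a null three-way term, or a Bayes Factor favouring its null, is not evidence that the two groups respond alike.
5. State that, without an untreated arm, group × session is a group difference in uncontrolled pre-to-peri change.

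The cost is wording and a few more tests per outcome, which makes the multiplicity correction somewhat heavier. No new data are needed. The terms come from the planned model, provided it carries the full set of interactions among group, session and intervention.

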## Abstract

**Background:**

Major Depressive Disorder (MDD) is one of the most prevalent psychiatric disorders, and involves high relapse rates in which persistent negative thinking and rumination (i.e., perseverative cognition [PC]) play an important role. Positive fantasizing and mindfulness are common evidence-based psychological interventions that have been shown to effectively reduce PC and subsequent depressive relapse. How the interventions cause changes in PC over time, is unknown, but likely differ between the two. Whereas fantasizing may change the valence of thought content, mindfulness may operate through disengaging from automatic thought patterns. Comparing mechanisms of both interventions in a clinical sample and a non-clinical sample can give insight into the effectivity of interventions for different individuals. The current study aims to 1) test whether momentary psychological and psychophysiological indices of PC are differentially affected by positive fantasizing versus mindfulness-based interventions, 2) test whether the mechanisms of change by which fantasizing and mindfulness affect PC differ between remitted MDD versus never-depressed (ND) individuals, and 3) explore potential moderators of the main effects of the two interventions (i.e., what works for whom).

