The current study will combine momentary-, behavioural-, cognitive-, and physiological measures at different timescales, which could give insight into the manifestations and dynamics of PC and how it can be modified by interventions. The effects of positive fantasizing and mindfulness will be contrasted by means of affect, cognition and physiology, all sampled at high temporal density, to see whether those can clarify different mechanisms for reducing PC. Whereas positive fantasizing is potent in reducing PC by using positive phantasy to enhance positive affect and positive cognitions, mindfulness focusses on increasing awareness of the present moment and is therefore potent in reducing PC. Additionally, we will characterize sleep patterns using actigraphy and self-report. Previously, PC has been found associated with poor sleep quality and sleep onset latency, which in itself can increase PC [40]. By including individual characteristic variables (such as personality, depressive history, and childhood trauma) as potential moderators of the main effect of intervention on PC, we can gain insight in what intervention works best for whom. This could be a step towards better personalized treatment [41]. The overall aim of the current study is to study the mechanisms by which mindfulness and positive fantasizing may affect the content and dynamics of PC and thereby contribute to lower depressive relapse vulnerability. The study has three objectives.

The first objective is to study the differential mechanisms by which mindfulness and positive fantasizing affect PC in individuals vulnerable for depressive relapse. To this end, we will randomize 50 remitted MDD (rMDD) individuals in a cross-over study to both mindfulness and fantasizing, with the order of interventions randomized over participants and the same duration of the interventions. We hypothesize that both techniques change PC but that they exert these effects differently. Specifically, we expect positive fantasizing to obtain its effects by increasing positive affect and changing the content of thoughts and expect mindfulness to obtain its effects by increasing focus on the present moment.

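### Aim 3 admits moderators through a correlation with change pooled over both groups, a screen that does not ask which intervention suits whom

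*Protocol article*

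**What the plan says.** The purpose of Aim 3 is put in comparative terms in the Background: "we can gain insight in what intervention works best for whom". The Conclusion of the article repeats that wording in substance. The abstract describes the aim as to "explore potential moderators of the main effects of the two interventions (i.e., what works for whom", and the third objective asks "whether individual characteristics affect the effectiveness of the two interventions in reducing PC across all participants".

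The population is both groups together. Outcome measures, Study aim 3 opens with "Baseline individual characteristics of 100 participants (both ND and rMDD".

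The method is in Statistical analyses, Study aim 3. The authors take the questionnaire-based characteristics "and correlate those with changes in 1) self-reported measures of PC measured with ESM and the SART", and likewise with changes in HR/HRV and EEG, after the two interventions. Then: "When significant correlations are found, we will do post-hoc moderation analyses" "to see how specific individual characteristics moderate changes in PC".

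No characteristic x intervention term and no group term is named for Aim 3. Aims 1 and 2, in the same section, do name their interaction terms. The third objective is labelled exploratory, and Benjamini–Hochberg applies to all analyses.

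**The concern.** Which intervention suits whom is a question about a difference between two effects, so the matching test is characteristic x intervention on the pre-to-peri change. The stated rule puts a different test in front of it. A characteristic that predicts change equally under both interventions passes the gate although it is no guide to choosing between them. A characteristic that helps under one and hinders under the other can be stopped before anyone tests it. The Background's own examples are of the second kind in spirit: anhedonia as an obstacle to fantasizing, low mental flexibility as an obstacle to mindfulness.

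Pooling adds a second route to a misleading result. If a characteristic and the change in PC both differ between rMDD and ND participants, they correlate in the pooled sample even when they are unrelated within each group. The resulting list could mix group differences, general prognosis and true differential response, and the article intends to draw lessons for personalised relapse prevention from it.

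**Working it through.** The article gives no power or error figure for Aim 3, so there is none to reproduce. The checks below show what the rule does.

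**Inputs from the article.** 50 participants per group for ESM, SART and questionnaires, so n = 100. 25 per group for EEG and ECG/ICG, so n = 50 (COVID-19 section). Alpha 0.05. Baseline rumination gap between rMDD and controls d = 0.686 (Sample size).

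**Assumptions.** Standardised characteristic; change under each intervention with residual SD 1; correlation ρ = 0.3 between a person's two residual changes; slopes as stated; two-sided single tests before Benjamini–Hochberg. Power ≈ Φ(atanh(r)·√(n−3) − 1.96), with √97 = 9.849. Rates for at least one of two separate correlations being significant come from simulation (4,000 runs).

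**1. Equal slopes of 0.3, so no differential effect, n = 100.**
- Combined change: r = 0.3/√(0.09 + (1+ρ)/2) = 0.3/√0.74 = 0.349. atanh = 0.364; 0.364 × 9.849 = 3.585; power Φ(1.625) = 95%.
- Separate correlations: each r = 0.3/√1.09 = 0.287, power about 83%. At least one is significant in 95%.
- Direct interaction test (correlation with the within-person difference of the two changes): true slope 0, flagged in 5 to 6%.

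**2. Opposite slopes +0.2 and −0.2, a true differential moderator, n = 100.**
- Combined change: mean slope 0, so the gate opens in 5%.
- Separate correlations: each r = 0.2/√1.04 = 0.196, power about 50%. At least one is significant in 79%. In 14% of trials the direct test is significant but the gate stays shut.
- Direct test: r = 0.4/√(0.16 + 2(1−ρ)) = 0.4/√1.56 = 0.320. atanh = 0.332; 0.332 × 9.849 = 3.27; power Φ(1.31) = 90% (91% simulated).

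**Sensitivity to ρ, n = 100.**

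| Quantity | ρ = 0 | ρ = 0.3 | ρ = 0.6 |
|---|---|---|---|
| Equal slopes 0.3, combined gate opens | 0.3/√0.59 = 0.391: 98% | 95% | 0.3/√0.89 = 0.318: 90% |
| Slopes ±0.2, direct test | 0.4/√2.16 = 0.272: 79% | 90% | 0.4/√0.96 = 0.408: 99% |

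At ρ = 0 separate correlations would open the gate for ±0.2 in about 1 − 0.5² = 75%, close to the direct test's 79%. On that reading the loss of true moderators is small unless the two changes are correlated. The passing of non-differential characteristics remains.

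**3. n = 50 (HR/HRV, EEG), ρ = 0.3.** Slopes ±0.2: the gate opens in 51% (separate) or 5% (combined); the direct test detects 64%. Equal slopes of 0.3: the gate opens in 73% or 72%; the direct test flags 5%.

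**4. Group membership alone.** With no within-group association, pooled r = (dx·dy/4)/√((1 + dx²/4)(1 + dy²/4)). Take dx = 0.686 and assumed change gaps dy.
- dy = 0.2: r = 0.0343/√(1.1176 × 1.01) = 0.032. Rejected in 6% at n = 100 and 6% at n = 50.
- dy = 0.5: r = 0.0858/√(1.1176 × 1.0625) = 0.079. Rejected in 12% at n = 100 and 8% at n = 50.

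In the simulations, adjusting for group returned the rate to about 5%.

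Psychiatric history, another listed predictor, is tied to group by eligibility: ND participants may have no lifetime psychopathology, and rMDD participants need at least two depressive episodes.

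**The case against.** The strongest reply is that the correlation is only a screen and the moderation analysis is the test. That model is not specified in a condensed article, and it could contain intervention and group. If it contained characteristic x intervention, the gate would not inflate false differential moderators: an equal-slope characteristic would pass both steps in roughly 3.5 to 5% of trials. This stands, and the 95% is the rate at which the gate opens, not a rate of false final claims. But the follow-up is described only as moderation of changes in PC, and it is reached only through the gate, so the loss of true moderators would remain.

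The abstract's phrase about moderators of main effects, and the objective's reference to all participants, also show that pooling is deliberate and that the question is not worded in one way only. That is fair, but the same aim is described as finding which intervention works best for whom, and group confounding affects either question.

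Several stronger readings are tempting and are not supported:
- A reader might infer that each intervention is correlated separately and that one significant and one non-significant result will be read as moderation. The article does not say so. It does not say that change is combined either, or that the difference between the two changes is used. On that last reading the gate would itself be the right contrast, but nothing in the text points to it.
- A reader might infer that the groups are selected on dysfunctional attitudes and rumination. Eligibility concerns depressive episodes, IDS-SR30 score and lifetime psychopathology.
- A group-driven rejection rate as high as 40% needs a predictor gap of 2.0 SD, which the article does not give.
- The article says that effects may differ in ND participants. It does not predict a change gap of any size.

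**Conclusion.** The concern holds in this form: the screen tests association with change, whereas the stated purpose is a comparison between interventions, and the pooled correlation takes no stated account of group. The mismatch is present whether correlations are per intervention or on combined change. It is severe for combined change, where an opposite-slope moderator is almost always lost, and milder for separate correlations. The inflation from pooling is modest at the only predictor gap the article cites.

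The rates depend on assumed slopes, change gaps and ρ, and are before multiplicity correction. Benjamini–Hochberg would lower the rates but would not change which question is tested, nor remove confounding by group. Because the aim is openly exploratory and no sample size depends on it, this is a moderate point: worth changing, without bearing on Aims 1 and 2.

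**What to change.** Drop the correlation gate. For each listed characteristic, fit the mixed model already planned, with characteristic x session x intervention as the moderation test. Include group and its interactions with session and intervention. Analyse psychiatric (depressive) history in rMDD participants only, since eligibility leaves it almost no variation in ND participants. Apply Benjamini–Hochberg to this set of interaction tests and report the correlations as descriptive. State n = 50 for the HR/HRV and EEG outcomes of Aim 3, because the figure of 100 in Outcome measures does not apply to them after the COVID-19 changes.

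The cost is wording and somewhat more modelling, with no additional measurements. There will probably be fewer nominally significant moderators, and at n = 50 power is limited (64% for slopes of ±0.2 under the assumptions above).
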